## Project 2: to identify neuroimaging biomarkers associated with domains of EF and SUD symptoms most predictive of functional outcomes

### Background

Whereas Project 1 (P1) will identify EF deficits that may be potential targets of cognitive interventions in future work, Project 2 (P2) will identify neuroimaging biomarkers associated with the same core EF domains and functional outcomes evaluated in P1 to inform innovative brain-based treatments for SUDs. To do so, a complementary mechanistic understanding of neural system dysfunctions that underlie behavioral EF deficits is needed.

Functional magnetic resonance imaging (fMRI) studies in healthy adults suggest that the three dimensions of EF have both common and distinct neural substrates. Studies investigating the three EF domains side by side show overlapping activation in frontoparietal regions, most notably the inferior frontal gyrus, anterior cingulate cortex and bilateral parietal cortices (92). The ability to maintain a task goal stably, shared across all EF domains, in turn relies on areas of the lateral prefrontal cortex (PFC) (30, 93, 94), anterior cingulate cortex (ACC) and frontal operculum (95).

In contrast, inhibition is associated with more extensive recruitment of temporal regions and the cortico-striatal circuit (96). Set-shifting may uniquely involve more posterior dlPFC regions and more extensive parietal areas (97, 98). Working memory updating has been additionally mapped onto fronto-striatal connections and requires input from the basal ganglia and cerebellum (99–101). Similar partially dissociable signatures of the three distinct EF dimensions have been identified in studies using resting-state (i.e., task-free) fMRI (102, 103), structural MRI (104, 105), and diffusion-weighted imaging (DWI) (104).

Meta-analyses of task-based fMRI across SUDs show altered activation in frontoparietal and striatal regions across studies (106). Importantly, however, prior studies have almost universally focused on a single EF domain, providing relatively limited insight into the complex cognitive architecture that may underlie EF impairment in SUDs (107–109). Clinically relevant insight is further limited by a predominance of cross-sectional studies, which do not investigate how neural features supporting EF may contribute to symptom change and functional recovery over time. Characterizing executive dysfunction heterogeneities and underlying neural circuits longitudinally across large naturalistic cohorts of patients seeking treatment for SUDs is likely to provide novel insight into the pathophysiology of addiction and help identify novel targets for brain-based interventions.

### Objectives

The first objective of P2 is to identify novel imaging biomarkers (MRI, fMRI) uniquely associated with each of the three domains of EF in SUDs. Its second objective is to identify relationships between these neurostructural and functional markers and SUD severity and day-to-day functioning, both cross-sectionally and over a one-year follow-up. These imaging biomarkers may help guide future development and individualization of biologically informed treatments for SUDs, e.g., through neuromodulation (see P4) or pharmacotherapies (see P5).

#### H2a

Behavioral performance on the three EF domains will map onto partially dissociable neural substrates overlapping with frontoparietal and corticostriatal circuits. The extent of activation and pattern of brain activity associated with each of the three EFs will be associated with greater SUD severity and lower general functioning at baseline.

#### H2b

Greater disturbances in EF-associated neural circuits at baseline will be associated with lesser improvement in SUD severity and functional outcomes on follow-up, above and beyond impairments in other neural circuits.

### Methods and planned analyses

#### Participants

All participants included in the total sample are invited to participate in a 1.5-hour MRI protocol. P2-specific exclusion criteria include the presence of MRI-incompatible metal implants, history of stroke, and claustrophobia. We anticipate approximately 50% of the entire sample (n=200) will be eligible and consent to MRI. Eligible participants are invited for a longitudinal scan at one-year follow-up; we anticipate 25% (n=50) being available and consenting to the repeat scan to assess longitudinal stability of our main measures. Given the specific safety requirements of MRI, it is possible that the final P2 sample will not be fully representative of the P1 sample in terms of demographics and clinical characteristics. If this is the case, we will consider this important caveat in interpreting any results using joint P1-P2 and conduct sensitivity analyses where appropriate.

#### MRI methods

Our research imaging protocol uses state-of-the-art imaging sequences fully harmonized with MRI acquisition protocols used by large-scale population-representative studies (110) and other ongoing CAMH-based cohort studies (111, 112) (see **Table 2**), which will allow us to leverage our data for comparison or transdiagnostic analyses. To support new research studies, a portion of the scanning time is secured for pilot sequences.

**Table 2 T2:** MRI sequences.

Whole-brain MRI Sequence	Duration (minutes)	Measure	Technical Parameters
3D T1 Magnetization Prepared RApid Gradient Echo (MPRAGE)	6:11	Total, interhemispheric, and/or regional cortical thickness (mm), cortical surface area (mm^2^), total and regional brain volume (mm^3^)	Field of view (FOV) 256 x 256 mm^2^ TR = 6.952 ms TE = 2.920 ms TI = 1060 ms 1 mm isotropic voxel size Parallel imaging factor ARC = 2 Slices per 3D slab = 208
Axial resting state functional MRI (fMRI)	10:00	Resting-state connectivity	FOV 216 x 216 mm^2^ TR = 800 ms TE = 30 ms Number of slices = 60 (no gap) Flip angle = 52° Matrix 90 x 90 2.4 mm isotropic voxel size Hyperband multi-slice acceleration factor = 6 Run time points 750
Axial N-Back fMRI	9:40	Executive Functioning: working memory	Same parameters as before Run time 725
Axial GoNoGo fMRI	7:16	Executive Functioning: inhibition	545
Axial Letter Judgement Task fMRI	7:36	Executive Functioning: set-shifting	570
Axial Diffusion MRI	7:11	Brain tissue microstructure	FOV 240 x 240 mm^2^ TR = 4100 ms TE = 81.7 ms Number of slices = 81 (no gap) Matrix 140 x 140 b-values (directions): b0 (8), b=500 s/mm^2^ (6), b=1000 s/mm^2^ (15), b=2000 s/mm^2^ (15), b=3000 s/mm^2^ (30) Hyperband multi-slice acceleration factor = 3
Oblique Axial Neuromelanin GRE	8:01	NeuroMelanin Sensitive MRI	Partial brain coverage with FOV = 165 x 220 mm^2^ TR = 284 ms TE = 4.1 ms Number of slices = 10 Slice thickness = 2.5 mm Slice gap = 0 mm Flip angle = 50° Matrix = 320 × 512

##### Structural measures

A standard T1-weighted structural scan is acquired to obtain detailed measures of cortical morphology (e.g., thickness, surface area, and volume). Diffusion-weighted imaging (DWI) is acquired to measure white matter tract integrity and tissue microstructure. Neuromelanin-sensitive (NM-MRI) scans are acquired to quantify the integrity of the substantia nigra (113, 114), with partial coverage of the locus coeruleus (115). NM-MRI scans were included to capture metrics related to catecholamine (i.e., dopamine and norepinephrine) signaling implicated in EF (116), and SUDs (113, 117), based on molecular imaging and preclinical models (118). NM-MRI captures the integrity of brain nuclei and neuromodulatory systems that are relatively conserved across species (119, 120). Thus, it also represents a unique bridge to the preclinical component of CDiA as described in Project 5 below.

##### Resting-state BOLD

Participants are asked to remain awake with their eyes open for 10 minutes while lying restfully in the scanner.

##### Cognitive fMRI paradigms

We administer three EF tasks for a total duration of ~30 minutes. The tasks assess the same EF domains as in P1 but were specifically selected to be distinct from the paradigms used in P1 to reduce practice effects, which may alter in-scanner performance and brain activation patterns (121, 122). The EF cognitive paradigms were adapted from Rieck et al. (92) and are presented in a pseudorandom order counterbalanced across participants. To minimize visual distraction and permit joint analysis across all EF dimensions, the tasks were designed to be visually simple and consistent across EF domains, using white or light-colored letter stimuli against a dark grey background (**Figure 2**).

**Figure 2 f2:**
[figure not shown]
Overview of fMRI tasks. **(A)**
Go-NoGo: Participants are shown a series of letters, one at a time, on a monitor, and are instructed to respond when they see the letter 'Y' (Go Condition) and not to respond (No Go Condition) to other letters. The task comprises two blocks with 90 Go Conditions and 30 No Go Conditions (75% Go and 25% No Go). **(B)** .Letter Judgement Task: Participants view one of two possible conditions and are instructed to indicate whether a letter presented on the screen is uppercase or lowercase, or whether it is a vowel or a consonant, respectively. The task comprises a single block with 30 switch trials, where the instructions on the current trial are different from the preceeding one and 30 repeat trials in which the instructions on the current trial match the preceeding one. **(C)** .N-back:The participant is shown a sequence of letters and is instructed to respond when the letter on the monitor matches the letter presented 2 trials earlier (2-back condition). The tasks consists of three blocks of the 2-back condition and three blocks of a 0-back condition, where participants are instructed to press a button when the letter X is presented (not visualized).

##### Proposed analysis

At baseline, task-based brain activation and brain structure will be investigated in association with SUD symptom severity, functional ability and out-of-scanner EF performance as measured by P1. Multivariate approaches (e.g., Partial Least Squares regression) will be used to investigate relationships between brain structure, function, and performance across the three EF tasks by identifying latent variables (LV) that capture covariance between the set of predictors (microstructure, performance) and outcome variables (functional activation). Individual brain scores reflecting the degree to which participants expressed the LV activation pattern will be correlated with SUD severity, functional ability and out-of-scanner EF performance, at baseline and on follow-up, uncovering neural factors crucial for improved functional outcomes. Age, sex, and primary substance of concern will be used as covariates. We anticipate the EF-domain-specificity of the neuroimaging results will mirror patterns obtained using out-of-scanner EF measures in P1. Although it is challenging to provide a power estimate for studies involving complex multivariate analytic approaches in neuroimaging, our proposed sample size is consistent with recent empirically derived recommendations to enhance reproducibility in task-based fMRI research (123). These studies suggest that a sample size of n=120 is sufficient to obtain a test-retest voxel-wise correlation >0.80 across most paradigms. Thus, our proposed cross-sectional sample size of n=200, is in line with these recommendations. Further, based on standard power analysis tools, a sample size of 200 allows power of >0.80 to detect small effect sizes on the order of r=0.2 or Cohen’s d=0.2.

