### Power analysis and data analytic plan

Multiple regression will be used with the clinical, functional, and demographic factors entered as simultaneous predictors of each EF domain to test hypotheses about which factors are most strongly associated with specific EF domains (H1a and H1b).

For H1c, we will conduct latent profile analyses using domains of EF as indicators of discrete latent profiles of relative deficits and biases. We will then examine the prediction of membership in these latent profiles from substance use profiles.

For H1d, latent growth curve modeling will be used to model changes in substance use frequency, SUD severity, and functional outcomes over the follow up time points. Next, rate of change will be examined as a function of baseline EF (H1a) by regressing variability in the slopes for the growth factors on baseline EF deficits and biases. These will be included as simultaneous predictors in the model to examine the specific EF domains and biases that are most predictive of change in the clinical and functional outcomes.

For H1e, we will use a generalized linear mixed effects modelling approach. EF deficits and biases will be modelled as dependent variables and time will be entered as a within-subjects factor to determine if there is significant within-person change from baseline to one year follow up. Changes over time in SUD symptoms and functional outcomes will be modelled using the same approach, with changes in EFs included in the models as a time-varying predictor of changes in these outcomes.

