### Limitations

This Research Program is not without limitations. First and foremost, the sample in P1-P3 is by design expected to be heterogeneous in terms of specific substance use profiles and comorbid diagnoses. At the same time, given the different eligibility requirements and diversity of methods (e.g., MRI safety requirements in P2), not all Projects’ samples will be representative of the full CDiA cohort. Notably, P4 and P5 represent smaller experimental studies targeting specific biological mechanisms and use narrower clinical phenotypes. Second, we recognize that the 12-hour abstinence window used in P1-P3 may not account for all residual effects of recently used alcohol or other substances on cognition. To account for this residual variability, all analyses will control for data on recency of use, collected through various means such as self-report and urine drug screens (**Table 1**).

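### Project 2's H2b is about improvement and value beyond other circuits, but the stated follow-up correlation, on its plain reading, tests neither

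*Protocol article*

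**What the plan says.** Project 2, H2b has two parts. The first concerns change: "Greater disturbances in EF-associated neural circuits at baseline will be associated with lesser improvement in SUD severity and functional outcomes on follow-up". The second concerns specificity: the relation should hold "above and beyond impairments in other neural circuits".

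The only follow-up analysis described for Project 2 is in its Proposed analysis section. Individual brain scores from the multivariate model "will be correlated with SUD severity, functional ability and out-of-scanner EF performance, at baseline and on follow-up". The same sentence attaches the interpretation, "uncovering neural factors crucial for improved functional outcomes". The covariate statement follows: "Age, sex, and primary substance of concern will be used as covariates". The Limitations section adds, for the whole programme, that "all analyses will control for data on recency of use".

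H2a expects the same activation measures to be related to SUD severity and functioning at baseline.

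Project 1, by contrast, does model change. Its plan for H1d is "regressing variability in the slopes for the growth factors on baseline EF deficits and biases". Project 2 does not refer to that model.

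**The concern.** A correlation between a baseline brain score and an outcome measured a year later mixes two things: the association already present at baseline, carried forward because the outcome is stable, and any association with change. H2b concerns the second alone. With no baseline outcome value, change score or slope named, the described analysis cannot separate them. Because H2a expects the first to be present, a positive follow-up correlation is likely even if the brain score says nothing about recovery.

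The specificity part of H2b has a separate gap. No comparison circuit, covariate or nested model in Project 2 addresses it, however the follow-up phrase is read.

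At stake is Project 2's main longitudinal claim. Its Objectives section says the imaging markers may guide the development and individualisation of treatments. A correlate of baseline status taken for a predictor of recovery would mislead that later work.

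**Working it through.** **Inputs from the article.** n=200 with baseline MRI (Project 2, Participants). Effect size r=0.2 with power above 0.80 (Project 2, Proposed analysis).

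**Assumptions.** Two-sided alpha 0.05, which is not stated for Project 2 (Project 3 uses 0.05). Baseline brain-outcome correlation r and 12-month outcome stability s are not given. I take r=0.2, the effect size in the power statement, and r=0.3, with s from 0.5 to 0.7.

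**Step 1: reproduce the plan's figure.** By Fisher z, power ≈ Φ(atanh(r)·√(n−3) − 1.96). For r=0.2 and n=200, atanh(0.2)·√197 = 2.845, and Φ(0.885) = 0.81. The stated power reproduces, but it is power for a simple correlation, not for H2b.

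**Step 2: what the planned correlation does when there is nothing beyond baseline.** If the brain score is unrelated to follow-up once the baseline outcome is known, the expected follow-up correlation is r·s. The chance of significance is Φ(z − 1.96) + Φ(−z − 1.96), with z = atanh(r·s)·√(n−3).

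| r | s | r·s | z (n=200) | Significant, n=200 | Significant, n=160 |
|---|---|---|---|---|---|
| 0.2 | 0.5 | 0.10 | 1.41 | 29% | 24% |
| 0.2 | 0.6 | 0.12 | 1.69 | 39% | 33% |
| 0.2 | 0.7 | 0.14 | 1.98 | 51% | 42% |
| 0.3 | 0.5 | 0.15 | 2.12 | 56% | 47% |
| 0.3 | 0.6 | 0.18 | 2.55 | 72% | 63% |
| 0.3 | 0.7 | 0.21 | 2.99 | 85% | 76% |

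The n=160 column assumes 20% loss. At r=0.1 and s of 0.5 to 0.6, the n=200 figure is 11% to 13%. A simulation of 20,000 runs at each corner of the n=200 grid gave 29%, 51%, 57% and 85%. Adding the baseline outcome to the model gave 4.9% to 5.0%.

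**Step 3: a different null.** If instead the change score is unrelated to the brain score (equal variances), the expected follow-up correlation is r itself. The planned test then rejects in 81% (r=0.2) or 99% (r=0.3) at n=200, and the change-score test in about 5%.

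**Step 4: the two ways of analysing change differ.** In the same simulations at n=200, the change-score test rejects in 19% to 57% under the null of Step 2. The baseline-adjusted test rejects in 22% to 73% under the null of Step 3. The choice therefore has to be made in advance.

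**Step 5: limit of baseline adjustment.** The 5% in Step 2 assumes a baseline outcome measured without error. With baseline reliability R and observed r and s, the follow-up correlation under the null is r·s/R. The partial correlation is (r·s/R − r·s)/√[(1−r²)(1−s²)]. For r=0.3 and s=0.6:

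- R=0.8: (0.225 − 0.180)/0.763 = 0.059, significant in about 13% of studies.
- R=0.7: (0.257 − 0.180)/0.763 = 0.101, significant in about 30% of studies.

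At r=0.2 the corresponding figures are about 8% and 15%.

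**The case against.** The strongest reply is that the article does not say the follow-up correlation uses outcome status. H2b uses the same follow-up phrase for improvement, and the analysis sentence ends by speaking of improved outcomes, so a change score cannot be excluded. This stands as a limit on certainty. The sentence nevertheless lists the same variables at both time points, so status at each is the plain reading. If change was meant, the article should say so and say which form.

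A second reply is that one paragraph in an article covering seven projects leaves covariates and comparison circuits to the full protocol. This stands in part: the covariate list is not presented as complete. But the article does state a test, covariates and an interpretation, and together these do not match H2b.

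A third is that Project 2's second objective, relating markers to severity and functioning over one year, is properly served by correlation with later status. That is correct. The fault lies only in treating that correlation as the test of H2b.

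A reader might also infer that adjustment is for age, sex and primary substance alone. The Limitations section adds recency of use, although that does not supply the missing baseline outcome. A reader might take the 72% cell as the error rate, but it rests on an assumed r=0.3. At the article's own r=0.2 and the same stability the figure is 39%.

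**Conclusion.** The concern holds as a mismatch between hypothesis and stated analysis. On its plain reading, the follow-up correlation can be significant through outcome stability alone and then be interpreted as bearing on improvement. The specificity part of H2b has no stated test on any reading.

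With n=200, two-sided 0.05, stability of 0.5 to 0.7 and no association beyond baseline, the false lead arises in about 29% to 51% of studies at r=0.2 and 56% to 85% at r=0.3. The values of r and stability are assumptions, and a smaller r or attrition lowers the figures.

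The documents do not support the stronger reading that a stable baseline association is bound to be reported as prediction of change. That depends on r, on stability, and on whether status was really meant.

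**What to change.** State in Project 2 that H2b is tested by regressing the 12-month outcome on the baseline brain score, with three additions:

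- the baseline value of the same outcome as a covariate;
- a pre-named non-EF circuit score from scans already acquired;
- age, sex, primary substance and recency of use, as now.

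Project 1's growth slopes for the outcomes measured bimonthly (Severity of Dependence Scale, WHODAS 2.0, WHOQOL-BREF) can be named as a secondary analysis. Fix the primary choice in advance, because the two answer different questions. Describe the unadjusted follow-up correlation as association with later status, not with improvement.

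The cost is wording only. The Project 1 schedule already collects these outcomes at baseline and year end, and the MRI protocol already includes resting-state, structural, diffusion and neuromelanin scans. There are two small downsides. Measurement error in the baseline outcome leaves some residual confounding, and the stated power for r=0.2 refers to a simple correlation, so it should not be quoted for the adjusted test of H2b.

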## Project 3: to identify biomarkers mechanistically associated with EF and functional outcomes in adult outpatients seeking treatment for SUD

### Background

Identifying neural biomarkers associated with EF in SUDs (P2) will provide valuable insight into neural mechanisms that may be targeted via brain-based therapies. However, imaging is relatively costly, not accessible to everyone (124, 125), and may offer limited insight into molecular mechanisms that may be targetable through pharmacological interventions. To address these limitations, Project 3 (P3) will assess peripheral blood-based biomarkers and provide insight into the molecular mechanisms underlying EF deficits in SUDs. The analysis of peripheral biomarkers has indeed emerged as a promising approach to probe potential mechanisms or inform prognosis for SUDs (126, 127). Establishing the relationship between peripheral biomarkers and cognitive dysfunction in SUDs can help to unravel contributing mechanisms, including domains of EF, and to understand associated risk and mediating factors.

Substance use can trigger the activation of microglia and astrocytes in the brain, driving their function to a neuroinflammatory response and inducing the production of pro-inflammatory biomarkers (128, 129). Several of these molecules can cross the blood-brain barrier, promoting immune activation in peripheral tissues. The persistence of this pro-inflammatory feedback loop between the brain and periphery can lead to reduced neuroplasticity, structural and functional changes in key neural circuits underlying cognitive and emotional processing, leading to executive dysfunction, physical disability, and a higher risk of SUD relapse (130) (**Figure 3**).

